#### Safety

Adverse events will be recorded throughout the course of the trial.

#### Process evaluation

Our embedded mixed methods process evaluation will aim to identify key issues and potential solutions to inform the design of a full-scale trial [47]. In particular, it will explore the effectiveness of recruitment pathways, the acceptability of the study design and intervention, and fidelity to the intervention protocol and training.

Mixed method approaches will include the following:Intervention logs completed by the therapists, which will include the number of young people attending, absences/partial attendance, and if planned activities went ahead.Observations of 10–15% of intervention sessions using an observation log to examine implementation and fidelity to the training and manual.Focus groups with therapists and support workers involved in intervention delivery (all staff will be invited, and we will carry out 1–2 focus groups per site). This will explore experiences of intervention training, delivery, and study processes.One focus group with the IM staff involved in delivery to gather experiences of running the intervention and any modifications that may be required or anticipated before progressing to a definitive trial.Focus group/interviews with referral partners to gather their experiences of referring their clients or service users to the intervention.Interviews or focus groups with approximately 24 women in total, aiming for 12 from each arm and equal numbers from both sites. These will explore their views on the acceptability of the intervention and study design and procedures, along with barriers and facilitators for engagement. They will be facilitated by someone of Islamic faith. Where possible, purposive sampling will be used to ensure diversity of experiences and perspectives.

The process evaluation draws on the Theoretical Framework of Acceptability (TFA; [69]) and will primarily explore retrospective acceptability via interviews and focus groups. Our intervention observations and intervention logs will also provide insight into concurrent acceptability, for example relating to opportunity costs (e.g. if participants are late to intervention sessions because of other commitments) and burden (e.g. issues with completion of homework).

Semi-structured topic guides will be developed for all focus groups and interviews. These will be informed by the TFA [69], and we will liaise with the Young Women’s Advisory Group (YWAG) as appropriate. For convenience, we anticipate interviews and focus groups will all be undertaken online but will be in accordance with participant preference.

### Data management

The database assigns participants with a unique participant identifier (PID) and all data will be recorded against this identifier. The database will be controlled, administered, and managed by the UHCTSN Data Management team. To maintain data quality, an audit trail will be maintained, allowing data queries to be raised, and missing data will be monitored. Further information can be found within the Data Management and Access Plan attached to our funding award (NIHR156425).

#### Statistical methods

Data analysis will be largely descriptive, reflecting the fact that this is a feasibility study where the aim is not to test the efficacy of the intervention but to assess the feasibility of conducting a larger scale trial. Based on our previous work [70], the referral, recruitment, and retention will be evaluated using standard reporting following the CONSORT [71, 72] criteria, reporting the proportions (and confidence intervals) of young people reaching each stage of the study, by referral source and study arm. Adherence will be assessed through the proportions of sessions attended and the extent to which young women continue to apply strategies learnt to improve mental health (survey data at 24 weeks). Feasibility of collecting outcome data will be evaluated by estimating the proportions of missing data in each of the outcomes assessed. The descriptive statistics of the outcome measures will be given by study arm, but no formal hypothesis testing will be undertaken. For the outcome measures, we will use the intention-to-treat population, i.e. individuals will be included if data are available in the study arm to which the group they are in was allocated regardless of attendance or compliance. As this is a feasibility study, no imputation of missing data will be carried out. To monitor safety, the number of adverse events (for example, a mental health episode triggered by the content of a session) will be reported by study arm along with the number of participants experiencing one or more events for individuals who attend at least one group session. Recruitment to the study will be monitored through the recruitment logs and reported using the standard CONSORT criteria for feasibility studies.

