### Trial design

A two-arm cluster randomised controlled feasibility trial delivered in groups in two locations (Birmingham and London). Clusters will each comprise 8–10 young Muslim women, with three groups at each site. This trial incorporates embedded mixed methods process evaluation.

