### Sample size

A sample size of 60 eligible young Muslim women from Birmingham and London (30 per site and 30 per arm) has been selected to enable 24 participants per arm at the final follow-up point, allowing for an estimated loss to follow-up of up to 20% (co-applicant GM’s study unpublished [58, 59]. This sample size allows for at least one IM-Adapted intervention group to be completed at each of the two study sites, giving six groups in total (3 intervention; 3 control). Each group is required to have 10 participants to ensure that at least 8 participants are present at any given session (allowing for 20% no show/drop out). As this is a feasibility study, the sample size is not powered to evaluate the efficacy of the intervention. A sample size of 60 participants will allow estimation of the completion rate to within a pre-specified level of precision of ± 10% assuming it is 90%, or ± 13% if it is 80%. We are confident that these are appropriate estimates and represent values that would allow progression to a full trial. The sample size is also in line with those for feasibility studies audited in the UK [60].

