## Methods: assignment of interventions

### Allocation

Participants will be recruited and placed sequentially into a group at each site; once the group at the site has reached 10 participants, the group will be allocated. The allocated treatment for a group will be automatically generated via the study database. Stratification will be by study site (Birmingham or London) with a block size of 2. The groups will be allocated by a process embedded in the web-based data management system REDCap [61, 62] managed by the University of Hertfordshire Clinical Trials Support Network (UHCTSN) ensuring allocation concealment. When a group is randomised, an email will be sent to the principal investigator (PI) and the Trial Manager, who will communicate with the Therapist and MHSW to set up the appropriate group sessions.

Due to the nature of the intervention, allocation blinding is not possible. Where possible, both supporting staff will be blinded during data collection and statistical analyses will be blinded. 

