#### Progression criteria

The following criteria have been developed to determine whether funding for a definitive trial will be sought, including items relating to recruitment, retention, adherence, and completion. This progression criteria follow a set of stop–go criteria (based on traffic light colours for the measures, where appropriate). Where traffic lights are used, green = progression (subject to a successful new funding application), amber = modifications and improvements required before progressing, and red = no progression to a future trial. For the non-traffic light measures listed below, a decision will be made based on the information available.Completion of key outcome measures (% of mental health and well-being measures completed):◦ Green: > = 80%◦ Amber: 51–79%◦ Red < = 50%.Participant engagement and attendance (% of planned sessions attended):◦ Green: > = 67%◦ Amber: 51 to 66%◦ Red: < = 50%Successful collection of resource use data (% of participants providing resource use data):◦ Green: > = 80%◦ Amber: 70–79%◦ Red: < 70%Adequate acceptability of interventions to young Muslim women.Professionals and support workers are willing to deliver sessions and encourage participant engagement.Sufficient referrals (with sufficiency based on the sample size required for a definitive trial, we will calculate from this feasibility study) received from various organisations for young people to participate in the trial.Recruitment is such that > = 10% of eligible screened participants are recruited.Appropriate outcomes measures are identified, including one potential primary outcome (> 75% of minimum important difference).Based on the estimated sample size, a necessary number of additional sites is identified for a definitive trial. No indication that the intervention is significantly less effective than usual care.No indication that the intervention has significantly increased the risk of adverse events compared to the control condition.

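### Progression turns on the intervention not being significantly less effective, but the plan names no between-arm estimate or interval to judge it, only descriptive summaries by arm

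*Protocol article*

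**What the plan says.** The Statistical methods section opens with "Data analysis will be largely descriptive, reflecting the fact that this is a feasibility study". On the outcome measures it says: "The descriptive statistics of the outcome measures will be given by study arm, but no formal hypothesis testing will be undertaken". Confidence intervals are promised there for the referral, recruitment and retention proportions, but no arm difference or interval is named for the outcome measures.

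The Progression criteria include "No indication that the intervention is significantly less effective than usual care" and "Appropriate outcomes measures are identified, including one potential primary outcome (> 75% of minimum important difference". Neither has traffic-light bands. For such items the section says: "For the non-traffic light measures listed below, a decision will be made based on the information available". The Outcomes section also lists early evidence of no clear inferiority among the primary feasibility outcomes.

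On layout, Trial design says: "Clusters will each comprise 8–10 young Muslim women, with three groups at each site". Sample size plans 30 women per site and 30 per arm, "giving six groups in total (3 intervention; 3 control"). Allocation says: "Stratification will be by study site (Birmingham or London) with a block size of 2".

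Table 2 schedules PHQ-9, GAD-7, WEMWBS, R-COPE, EQ-5D-5L and loneliness at T0, 6 weeks and 24 weeks. PHQ-9 is also taken at screening, before randomisation.

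**The concern.** A criterion worded in terms of significance needs either a test or an interval. The analysis section rules out the first for the outcome measures and does not mention the second. What remains is two columns of summary statistics from three groups each, to be read by eye.

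That reading is exposed in two ways. With so few groups, the arms can easily differ at entry by an amount that matters, and nothing in the stated analysis allows for it. And the planned numbers of groups per site and per arm cannot both hold without tilting each arm towards one site. A definitive trial could be discouraged, or a real warning missed, because of which groups fell in which arm.

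**Working it through.** **Inputs from the protocol.** Six groups, three per site and three per arm; 30 women per arm, 24 after 20% loss; block size 2 within site; PHQ-9 entry range 5 to 14.

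**Assumed, because the protocol gives no values.** ICC 0 to 0.05; baseline–follow-up correlation r = 0.3, 0.5 or 0.7; site difference 0.2 to 0.5 SD. All results are in SD units.

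**1. The plan's own figure.** 24 / (1 − 0.20) = 30 per arm, 60 in total. It reproduces.

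**2. Site layout.** With block size 2 and three groups at a site, the first two groups get one arm each and the third gets either. Across the two sites there are four equally likely outcomes:

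| Intervention:control, site A | Site B | Total | Share of intervention groups at A − share of control groups at A |
|---|---|---|---|
| 2:1 | 1:2 | 3:3 | 2/3 − 1/3 = +1/3 |
| 1:2 | 2:1 | 3:3 | 1/3 − 2/3 = −1/3 |
| 2:1 | 2:1 | 4:2 | 2/4 − 1/2 = 0 |
| 1:2 | 1:2 | 2:4 | 2/4 − 2/4 = 0 |

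In both 3:3 outcomes the plain arm difference contains one third of the site difference: 0.2/3 = 0.07, 0.3/3 = 0.10, 0.5/3 = 0.17 SD.

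**3. Standard error of the plain arm difference.** With 24 per arm in groups of 8, SE = √[(2/24)(1 + 7 × ICC)].
- ICC 0: √0.0833 = 0.289.
- ICC 0.05: √(0.0833 × 1.35) = 0.335.

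**4. Chance baseline imbalance.** The same SE applies to a standardised baseline score among those retained.
- ICC 0: 0.3/0.289 = 1.04, so P(|difference| > 0.3) = 0.30.
- ICC 0.05: 0.3/0.335 = 0.89, so P = 0.37.

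**5. Baseline adjustment alone.** SE is multiplied by √(1 − r²): 0.954, 0.866 and 0.714, which are cuts of about 5%, 13% and 29%. At ICC 0.05 this gives 0.320, 0.290 and 0.240. These are upper limits. If adjustment reduces only the within-group variation, the SEs are 0.325, 0.304 and 0.271.

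**6. Adding site, 3:3 layout.** In units of the variance of a group mean:
- Plain contrast: 1/3 + 1/3 = 0.667.
- Within-site contrast, sites weighted equally: ¼[(1/2 + 1) + (1 + 1/2)] = 0.75.
- The SE ratio is √(0.75/0.667) = 1.06, and between-group degrees of freedom fall from 4 to 3.
- At ICC 0.05, adjusting for both baseline and site gives SEs of 0.339, 0.308 and 0.254.

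**7. When site adjustment pays.** Let v be the variance of the plain contrast and d the site difference. Its mean squared error is v + (d/3)²; the site-adjusted one is 1.125v. They are equal at d = 3√(0.125v): 0.31 SD at ICC 0 and 0.36 SD at ICC 0.05, before baseline adjustment.

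**8. Width of a 95% interval at ICC 0.05.**
- Plain, 4 df: 2.776 × 0.335 = ±0.93 SD.
- Baseline-adjusted, r = 0.5, 4 df: 2.776 × 0.290 = ±0.81 SD.
- Baseline and site, r = 0.5, 3 df: 3.182 × 0.308 = ±0.98 SD.

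**The case against.** The strongest reply is that this is a feasibility study which disclaims both power and testing for efficacy. Its analysis is described as largely, not wholly, descriptive. Covariates are commonly settled in an analysis plan, which is not shown here, and tables by arm would normally show baseline scores. This stands in part: the protocol nowhere says that baseline or site will be left out of every summary, and the absence of a covariate list is not the defect. What the reply does not meet is that the protocol itself sets a criterion in terms of significance while excluding formal testing of the outcome measures and naming no estimate in its place.

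The site effect is also limited. It is one third of an unknown difference, has random sign with zero mean over randomisations, and vanishes in the 4:2 and 2:4 layouts that occur half the time. But 3:3 is the layout that Sample size plans, and an average of zero does not protect the single allocation that is realised.

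Three stronger readings are tempting and are not supported:
- *That both effect-related criteria will be decided on a raw arm difference crossing a line.* The protocol says only that the available information will be used. It does not say whether the 75% figure refers to an arm difference, a within-person change or an interval bound.
- *That ignoring site makes the contrast noisier.* Only ignoring baseline does; adjusting for site adds noise.
- *That full adjustment would bring a clear gain in power.* Take a true inferiority of 0.8 SD, ICC 0.05 and r = 0.5. The chance that a 95% interval excludes zero is 44% for the plain contrast (4 df) and 43% with baseline and site adjustment (3 df), if the sites do not differ.

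**Conclusion.** The point holds as a mismatch within the protocol: a progression criterion refers to a significant disadvantage, and the stated outcome analysis supplies nothing by which to judge one. By-arm summaries would also leave unaddressed a 30% to 37% chance of a baseline imbalance above 0.3 SD and, in the planned layout, a shift of 0.07 to 0.17 SD from site. These sizes rest on the assumed ICC and site difference.

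Baseline adjustment is the better-supported improvement, cutting the SE by up to about 5%, 13% or 29% at r = 0.3, 0.5 or 0.7. The gain is probably smaller for PHQ-9, whose entry range restricts its baseline spread. Site adjustment is a useful check rather than a clear gain, since it lowers mean squared error only if the sites differ by roughly 0.3 SD or more. With six groups no method settles effectiveness; that is a reason to show an interval, so that a chance difference is not read as inferiority.

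**What to change.** Keep the descriptive tables. In Statistical methods, add for each outcome at 6 and 24 weeks the between-arm difference adjusted for the baseline value of the same measure, with a confidence interval that respects the groups and no p-value. One way is to compare group means of baseline-adjusted residuals on a t reference with 4 df. For PHQ-9, use a pre-randomisation score. Table 2 places T0 after randomisation, so for the other measures also state whether T0 is completed before participants learn their allocation.

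Report the within-site estimate (3 df) beside it as a check.

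In Progression criteria, judge the less-effective criterion on the baseline-adjusted interval, replace 'significantly' with wording that matches, and say whether the 75% threshold is read from the same estimate and, if not, from what.

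The cost is a few sentences and a small amount of analysis. It needs no new participants or data and is compatible with the decision not to test hypotheses.

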#### Process evaluation

Qualitative focus group and interview data will be audio recorded and transcribed. If conducted online, Zoom transcription will be enabled and quality checked and corrected in conjunction with the audio recording. The data will be analysed using reflexive thematic analysis [73] on NVivo software. We will use both deductive coding (based on the Theoretical Framework of Acceptability) and inductive coding (to centre the experiences and perspectives of participants) to develop themes. This will provide insight into recruitment, engagement, and delivering and receiving the intervention. Data from the intervention logs and intervention observations will be compared against the intervention manual, and findings will be tabulated and summarised narratively to inform our understanding of fidelity to the training and how the intervention was delivered and received. Triangulation of the analysis of the focus groups and interviews, intervention observations, and intervention logs will be used to describe delivery of both arms and examine implementation fidelity and explore factors affecting engagement across study processes. This will inform the feasibility assessment of the study and refine the design and intervention for a future trial.

#### Economic evaluation

The methods required to evaluate cost-effectiveness of a future trial will be tested in this feasibility study. We will measure resources required to provide the IM-Adapted intervention and the comparator of psychoeducation group support in the two groups. Resources will include staff time, equipment and consumables, accommodation, and staff training. In addition to these resources, an effective intervention may affect the use of health and social care services, as well as costs borne by the young women and their families. These will be recorded by means of a resource use questionnaire (modified client service receipt inventory (CSRI)) at baseline and 24 weeks [68], which, at both baseline and follow-up, will ask about the previous 24-week period. This will also record important non-health-related resource implications, including employment, education, or training status and time off work or usual activities. The modified CSRI cover aspects related to non-health-related resource use, including employment status, time unemployed, time off work or usual activities. It will also cover health-related resource use of inpatient and secondary care services, community and primary care services, and use of medicines. Resource use categories were discussed with other members of the research team to ensure that the most relevant categories of relevant service use were covered. Part of this feasibility study will include an assessment of this instrument, including completeness and ease of use. Any resources identified by the CSRI will be costed using appropriate local and national cost data.

The main outcome measure for the economic evaluation in a future main study would be the Quality Adjusted Life Year (QALY). In the feasibility study we will estimate QALYs using the EQ-5D-5L, collected at baseline, 6 and 24 weeks [68], and scored using a published scoring algorithm [74]. In a future full economic analysis, the EQ-5D-5L would be used to generate QALYs using ‘area under the curve’. The EQ-5D-5L will be compared descriptively with other outcome measures used in the feasibility study. It is not intended to estimate cost-effectiveness from the feasibility study as the study will not be powered to demonstrate this. Rather, the aim is to trial the proposed health economics measures, ascertain their completeness and acceptability to respondents, and identify likely main drivers of costs.

## Methods: monitoring

### Data monitoring

Data monitoring and monitoring of participant safety will be allocated as a standing agenda item for the Trial Steering Committee (TSC). Where data monitoring indicates that serious harm might be occurring in more than two cases over the course of the study, a subgroup of the TSC will be asked to review the data and make recommendations relating to likely future risk to the study participants and the need for further independent scrutiny of the data.

### Harms

To monitor safety during the study, any adverse event (AE) occurring during the participation of the study will be reported in accordance with the study protocol and IM policies. We will monitor for any potential harm and unanticipated outcomes during the intervention and the 6-month follow-up period. Should an AE occur, the member of the study team who first becomes aware of the AE must record it on the database and assess whether the event is considered serious. All serious adverse events (SAEs) will be communicated to the PI and Trial Manager (or delegated person in their absence) within one working day using the provided SAE form on the database. The PI and Trial Manager will review the SAE form and disseminate it to the CI and the Trial Management Group (TMG) within 72 h of being informed, where appropriate. The TSC and Research Ethics Committee (REC) will be informed by the Trial Manager of all SAEs periodically unless the Chief Investigator (CI) escalates the SAE or deems it necessary.

### Auditing

Quality assurance activities will be conducted by the sponsor and UHCTSN. This will include following the UHCTSN quality management system and review of key documents. Central and site monitoring will be conducted during the course of the study. An onsite monitoring visit at each site will be conducted at least once during the study, and central monitoring of the database will occur throughout the study.

## Public involvement

Public involvement in the study is co-led by a member of the research team and a public co-applicant with relevant lived experience. Participative approaches are embedded throughout the project, including in the development of the proposal. This included a workshop in November 2022, attended by six women with relevant lived experience and supported by funding from the NIHR Research Design Service. This identified the need for young people’s involvement to be inclusive and flexible and to address issues about stigma, cultural sensitivities, and religious guilt. Fifteen young Muslim women aged 16 to 30, with lived experience of using mental health services, were identified through the authors’ networks and invited to attend an online workshop in November 2023. Ten attended and contributed to the development of plans for inclusive involvement in the study.

In Spring 2024, an invitation was sent out via the authors’ networks for UK-based young Muslim women, aged 18–30 and with lived experience of using mental health services and/or affected by mental health issues, to join a public advisory group. Twelve expressions of interest were received and the first meeting of the Young Women’s Advisory Group (YWAG) took place in April 2024. The group will meet every 2–3 months, depending on group members’ availability and the stage of the project. The meetings will mainly take place online, with the option for in-person or hybrid meetings/social events if this works for group members.

Training and support will be provided as needed. Members of the YWAG will also have opportunities for involvement outside of meetings (e.g. reviewing documents, attending events), as well as having two YWAG places on the TSC and being supported to have an active role in the process evaluation. Members of the YWAG will receive gift vouchers as a thank you for their involvement.

Public involvement in the study is overseen by a working group led by the public involvement lead and the public co-applicant, which includes the CI and trial manager. The group meets monthly to collectively ensure that plans for involvement are embedded throughout the project, are meaningful and effective, and reflect cultural sensitivities and lived experience, reporting regularly to the TMG and TSC. The public co-applicant will provide a ‘lived experience’ perspective throughout the project, working with the public involvement lead to plan and co-facilitate public involvement, and supporting and advising the research team on working in culturally sensitive and inclusive ways. We will also draw on support from the UH public involvement team and the NIHR Applied Research Collaboration East of England’s public involvement workstream where required.

